#### Exploratory outcomes

Health economics through cost-effectiveness will be determined via the EQ-5D-5L, which performs a cost-utility analysis (CUA) to assess the improvement of each treatment in quality-adjusted life years (QALYs), as recommended by the National Institute for Health and Clinical Excellence (NICE) [48]. The level of activity according to the UCLA activity score will be recorded.

The observational cohort for patients who decline randomization. These patients will receive standard treatment at their local department and receive questionnaires at the same timepoints as the randomized cohort.

## Patient and public involvement

In the absence of a fracture patient organization, we have had contact with the Patient Organization for Osteoporosis, South Sweden, who have been given opportunity to have opinions on the study protocol.

We conducted semistructured qualitative interviews with patients recently treated for a clavicle fracture at Uppsala University Hospital, to assess their experiences about the treatment and hear their thoughts on the gross outline of the ScanDiLaC study. In line with previous qualitative studies on fractures [49], more information was generally requested regarding both the fracture itself and the treatment options. All patients were positive about the ScanDiLaC study’s design and using a data collection platform like REDCap. Some suggested that questionnaires be available in physical form to maximize participation in the older population, as well as in a phone application or text messaging format, both of which are possible with REDCap.

With these qualitative data and support from a patient organization, we judge the study design to be well optimized for patient participation and to minimize drop-out. We will aim to have physical copies available for all questionnaires at follow-up visits at all recruitment sites.

## Statistical methods

### Hypothesis

Null hypothesis (H0): The DASH score at 1 year after nonsurgical treatment is inferior to surgical treatment with a plate ± CC fixation of displaced, extraarticular LCFs.

Alternative hypothesis (HA): The DASH score at 1 year after nonsurgical treatment is not inferior to surgical treatment with a plate ± CC fixation of displaced, extraarticular LCFs.

### Sample size

To make an accurate sample size prediction, estimates in standard deviation (SD) scores for the DASH were acquired for the study population. As we found no study that explicitly studied these values for the DASH in patients with LCFs, a number of sources were used, including several RCTs [27, 50–52], as well as studies on different populations of the USA [53], Norway [54], and Germany [55]. Using the numbers from the studies above, we estimated that the mean SD for DASH is 14.3 for those aged 18–65 years. The minimal clinically important difference (MCID) was estimated using an extensive literature review and estimated as 10.4 [37–39, 56–61].

A sample size calculation was performed by a biostatistician at Uppsala Clinical Research Center (UCR) for the study, assuming a 20% attrition rate (an estimate on the basis of data from the SWIFFT trial (where a similar multicenter, pragmatic design was used) [62], the FISH trial [50], and the SHAFT trial [51]).

Since we have limited data on the correlations between the baseline and on-treatment DASH values, we calculate power for an unadjusted t-test, which approximates the primary baseline-adjusted mixed-effect model under a pessimistic scenario and provides a conservative estimate. Assuming a noninferiority limit of 10.4 (MCID), a one-sided alpha of 0.025, 90% power, and SD values of 14.3, a study population of 80 is needed. With an expected attrition of 20%, the total population becomes 100. The calculations were performed via R v. 4.2.3 and the base stats package.

### Statistical analysis

The primary outcome is the DASH score at 1 year while under observation, regardless of deviations from assigned treatment or other concomitant treatments. The noninferiority limit will be tested at a 1-sided alpha = 0.025.

The primary analysis will use linear regression for all observed post-randomization measurements, with the participant as a random effect, and the baseline DASH score, randomized treatment, visit number, and the treatment–visit interaction as fixed covariates. The results are presented as the estimated mean difference in the DASH score at 1 year with 95% confidence intervals, the 1-sided *p* value for noninferiority, and the 2-sided *p* value for differences from zero.

The primary model is unbiased for data that are missing at random conditional on the treatment arm, baseline, and a normally distributed individual baseline- and visit-adjusted mean DASH. The impact of missing data will be investigated via sensitivity analyses, which assume a continuum of nonrandom differences between observed and missing data. No imputation will be used.

Supplementary analyses will target the biological efficacy of nonsurgical versus surgical treatment through adjusted per-protocol analyses.

Secondary outcomes will be interpreted as supportive of the primary and analyzed without formal multiplicity adjustment. DASH comparisons for nonprimary timepoints will be taken from the primary analysis. VAS data will be analyzed via the same method as the primary analysis (adjusting for their respective baseline). Likert-scale outcomes will be analyzed via proportional odds logit regression adjusted for baseline as a categorical variable, separately for each timepoint. Complications, radiographic healing, and return to work and activities will be presented descriptively. A detailed statistical analysis plan (SAP) will be finalized before analysis.

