#### Outcome timepoints

Outcome measures will be obtained at the following timepoints: preinjury, baseline, 6 weeks, 3 months, 6 months, 1 year, 2 years, and 5 years. Study follow-up visits for the ScanDiLaC study is seen below (Fig. 2).

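### The primary model, as described, pools DASH variance over visits, so the 1-year confidence interval may be miscalibrated and the sizing is not assured to be conservative for it

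*Protocol article*

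**What the plan says.** **Primary model.** The Statistical analysis section of the Protocol article says: "The primary analysis will use linear regression for all observed post-randomization measurements, with the participant as a random effect". The fixed terms are baseline DASH, treatment, visit and treatment by visit. The missing-at-random statement in that section is conditional on treatment arm, baseline and a single Gaussian mean per participant, which is how a random intercept is described. Residual covariance is not mentioned. A detailed SAP is to follow.

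**Decision rule.** "The noninferiority limit will be tested at a 1-sided alpha = 0.025".

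**Reuse of the model.** "DASH comparisons for nonprimary timepoints will be taken from the primary analysis". VAS pain is to be analysed by the same method.

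**Visits.** The Outcome timepoints section lists, after preinjury and baseline, "6 weeks, 3 months, 6 months, 1 year, 2 years, and 5 years". The abstract lists follow-up only to 1 year. The model description sets no last visit.

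**Sizing.** The Sample size section uses an unadjusted t-test, "which approximates the primary baseline-adjusted mixed-effect model under a pessimistic scenario and provides a conservative estimate". The reason given is limited data on how baseline and follow-up DASH correlate. The SD is a single value: "we estimated that the mean SD for DASH is 14.3 for those aged 18–65 years".

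**The concern.** A random intercept with one residual variance fixes the same SD at every visit and the same correlation between any two visits. The treatment-by-visit term keeps the 1-year point estimate unbiased with complete data. Its standard error, however, reflects the average variance over all visits in the model, not the variance at 1 year.

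Equal spread from 6 weeks to 1 year is a strong assumption in this setting. The 6-week visit will mix patients who have largely recovered with others in enough pain to be offered crossover surgery.

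Three things are at stake:

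- The noninferiority decision compares a confidence limit with 10.4, so an error in the scale of the standard error acts directly on that decision.
- The sizing t-test uses one SD and takes no account of pooling over visits. The argument that it is conservative covers baseline adjustment only.
- The DASH results at other visits come from the same fit, so an interval too wide at 1 year goes with one too narrow at a visit whose SD exceeds the pooled value.

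**Working it through.** **Inputs from the protocol.** Margin 10.4, one-sided alpha 0.025, power 90%, SD 14.3, 1:1 allocation, 20% attrition.

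**Assumed inputs.** SDs by visit, because the protocol gives none. They are listed as 6 weeks / 3 months / 6 months / 1 year.

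**Step 1: the plan's own figure.**

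n per arm = 2 × (1.960 + 1.282)² × 14.3² / 10.4² = 39.7, so 40 per arm and 80 in total; 80 / 0.8 = 100. The stated size reproduces. At 40 per arm the standard error is 14.3 × √(2/40) = 3.198, and power is Φ(10.4/3.198 − 1.96) = Φ(1.292) = 90.2%. The exact t-test gives 89.5%.

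**Step 2: standard error under a random intercept.** With complete balanced data:

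- pooled SD = √(mean of the squared visit SDs)
- model SE = pooled SD × √(2/40)
- true SE = 1-year SD × √(2/40)
- power at no true difference = Φ((10.4 − 1.96 × model SE) / true SE)
- one-sided error at the margin = Φ(−1.96 × model SE / true SE)

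Example for 20/18/16/14.3: (400 + 324 + 256 + 204.5)/4 = 296.1, so the pooled SD is 17.2. Model SE = 3.848, true SE = 3.198 and the ratio is 1.20. Power = Φ((10.4 − 7.542)/3.198) = Φ(0.894) = 81.4%. One-sided error = Φ(−2.359) = 0.9%.

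| Assumed SDs | Pooled SD | SE ratio | Power | One-sided error | Coverage |
|---|---|---|---|---|---|
| 14.3 at all visits | 14.3 | 1.00 | 90.2% | 2.5% | 95.0% |
| 18/16/15/14.3 | 15.9 | 1.11 | 85.9% | 1.5% | 97.1% |
| 20/18/16/14.3 | 17.2 | 1.20 | 81.4% | 0.9% | 98.2% |
| 12/12/13/14.3 | 12.9 | 0.90 | 93.2% | 3.9% | 92.2% |
| 18/15/13/11 | 14.5 | 1.32 | 95.0% | 0.5% | 99.0% |

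**Step 3: simulation.** Random-intercept REML fit, 50 per arm, 20% lost at random by 1 year, 1,500 runs per setting, no baseline correlation. Two correlation patterns were used: equal at 0.6, and decaying at 0.7 per visit step.

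| Assumed SDs | Power | One-sided error | Coverage |
|---|---|---|---|
| 14.3 at all visits | 90–92% | 2.1–2.7% | 94–95% |
| 18/16/15/14.3 | 86–88% | 1.3–1.6% | 97–98% |
| 20/18/16/14.3 | 83% | 0.4–1.1% | 98% |
| 12/12/13/14.3 | 94–95% | 3.4–3.8% | 91–92% |

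A t-test on 1-year completers kept 88–91% power throughout, so the shortfall comes from the pooled variance. Equal SDs with decaying correlation stayed close to nominal, so in these settings unequal variance is the main driver.

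**Step 4: baseline adjustment.** With a baseline correlation of 0.3 (decaying pattern), power was 90% for 18/16/15/14.3 and 86–87% for 20/18/16/14.3.

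**Step 5: other visits.** Under 20/18/16/14.3, the 6-week SE ratio is 17.2/20 = 0.86. The two-sided error there is 2 × Φ(−1.96 × 0.86) = about 9% instead of 5%.

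**Step 6: later visits.** Adding 2-year and 5-year data at an assumed SD of 13 to 20/18/16/14.3 gives a pooled SD of 15.9 and power of 86% (86–87% simulated). The 1-year interval therefore depends on which visits are in the data at analysis.

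**The case against.** **The residual covariance is unstated, and the SAP may settle it.** This is fair. A participant effect is compatible with visit-specific residual variances or a robust standard error, and such detail often sits in an SAP. But the protocol does describe the primary model, and both the single random effect and the missing-data condition read as a random intercept. The point is about the model as described.

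**A reader might infer that the 1-year interval is wrong and the power claim false.** The documents do not support that. They give no SD by visit, every sequence above is assumed, and equal SDs return nominal results. The direction is open too: falling SDs cost power, while rising SDs inflate the noninferiority error.

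**The 14.3 is not labelled a 1-year SD.** Correct. It is a mean over several trials and population studies. If it is nearer a pooled value, as in 18/15/13/11, power is 95% and the sizing is conservative after all.

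**The conservative statement concerns baseline adjustment only.** As an argument about baseline correlation it is sound, and the gain can offset part or all of the loss (step 4). It does not reach the pooling of variance.

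**Falling SDs make false noninferiority claims rarer, and the other DASH visits are only supportive.** Both stand, and they lower the severity. Adding later visits also raised power in the scenario tried, so an open-ended visit set is an ambiguity rather than a further loss.

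**Conclusion.** The point holds in conditional form, at moderate severity. As described, the primary model assumes a common DASH variance over visits. If SDs differ, the interval compared with 10.4 is miscalibrated:

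- **SDs falling to 14.3 at 1 year:** too wide, with power about 86% to 81% in the two assumed patterns before any baseline gain.
- **SDs rising to 14.3 at 1 year:** too narrow, with one-sided error about 3.4% to 3.9% in the assumed pattern.

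These sizes rest on the assumed SDs, a 1-year SD of 14.3 and a single residual variance. The stated 80 evaluable and 100 randomized are arithmetically right. What is not assured is that the t-test behind them is conservative for this model. It would be going too far to conclude that the trial is underpowered or that its type I error is inflated, since the documents fix neither the presence nor the sign of the effect.

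**What to change.** In the protocol wording and the SAP, before any outcome data are analysed:

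- Specify a repeated-measures model with categorical visit and an unstructured residual covariance over 6 weeks, 3 months, 6 months and 1 year. This has 4 variances and 6 covariances, so 10 parameters. Visit-specific residual variances, or a robust standard error, are the minimum alternatives.
- Prespecify a fallback structure in case the model does not converge.
- Limit the primary model to visits up to 1 year and analyse later visits separately.
- Use the same structure for VAS.
- Restrict the conservative statement in the Sample size section to baseline adjustment, or tie it to the revised model.

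Baseline-by-visit terms and Kenward-Roger degrees of freedom are optional refinements.

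The cost is wording, a few more covariance parameters and a possible convergence fallback. The sample size need not change: with the variance estimated at 1 year and an SD of 14.3 there, 80 evaluable patients still give about 90% power.

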#### Randomization

Research Electronic Data Capture (REDCap©) is a computerized database software hosted by Uppsala University [30]. It will be used to perform block randomization through an irreversibly random allocation sequence with selected block sizes of 2 and 4, stratified by site. Patients will be allocated in a 1:1 ratio between surgical and nonsurgical treatment. The trial worker who includes the patient will then acquire the allocated treatment from REDCap and initiate the treatment, either by scheduling the patient for surgery or commencing nonsurgical treatment according to the study protocol. The trial flowchart for the ScanDiLaC study is seen below (Fig. 1).

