## Discussion

The ScanDiLaC study will compare the effectiveness of surgical versus nonsurgical treatment of displaced Neer type II and V lateral clavicle fractures and attempt to define the appropriate timing of early crossover surgery. The optimal treatment for the unstable Neer types II and V is not clear from the literature.

The TSC made a mutual, pragmatic decision to not include patients above 65 years old in the study, as no one would consider performing primary surgical treatment for this age group.

To achieve sufficient power in this study, we would need to ensure an adequate inclusion rate. In 2024, 320 displaced LCFs were registered in the Swedish Fracture Register [64] across all of Sweden. If only the currently recruiting sites are included and consider the possibility of incorrectly registered fractures [65], as well as the expected success rate of inclusion for each patient, we have estimated an optimistic possible inclusion rate of 31–32 patients per year in Sweden. We expect that the number will be matched when Denmark, Norway, and Finland are combined. This emphasizes the need for this multicenter collaboration between Nordic countries, where there are comparable healthcare systems and cultural and demographic similarities. Despite this, there are local differences in treatment, particularly with surgical treatment, where the use of hook plates has been a topic of much debate among orthopedic surgeons [18–21]. Many sites use hook plates, whereas others do not. This leads us to take a more pragmatic approach and allow both hook plates and anatomical locking plates with or without CC fixation. Since most surgeons consider removal of the hook plate after bony healing to be a mandatory part of the treatment algorithm [19], this will not be considered a complication in the context of this study.

Given the possibility of surgical treatment differing between sites, there is a risk of bias in the surgical group where it would be possible that a single site only randomizes to surgical treatment. To minimize this risk, the randomization will be stratified by sites in smaller permuted blocks of 2 and 4 to limit the risk of open blocks in multiple sites, as the expected number of patients included per site is low. This reduces the risk of allocation bias.

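### Randomisation is stratified by site but the primary model has no site term, so its interval is slightly too wide if sites differ (conservative, minor)

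*Protocol article*

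**What the plan says.** The Randomization section of the protocol article allocates 1:1 in permuted blocks, "with selected block sizes of 2 and 4, stratified by site". No other stratification factor is named.

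The Statistical analysis section specifies the primary model as a regression on all post-randomisation DASH measurements "with the participant as a random effect" and "the baseline DASH score, randomized treatment, visit number, and the treatment–visit interaction as fixed covariates". Site appears in neither the random nor the fixed part. VAS is to be analysed by the same method. The Likert-scale outcomes get proportional odds models adjusted for baseline only, one per timepoint.

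The Discussion gives the reason for stratifying: "Given the possibility of surgical treatment differing between sites, there is a risk of bias in the surgical group". It adds, on fixation, "Many sites use hook plates, whereas others do not", and notes that "the expected number of patients included per site is low". The Sample size section bases power on an unadjusted t-test and calls that conservative. A detailed SAP is to be finalised before analysis.

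**The concern.** Blocking within site keeps the arms nearly balanced within each site. Differences in mean DASH between sites then largely cancel from the treatment contrast, and its true variance is smaller than under unrestricted randomisation. A model without site does not know this. It counts between-site variation as patient-to-patient variation and carries it into the standard error. The participant random effect does not help, because treatment is compared between participants and the site variance is simply absorbed into the participant variance.

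Some site variation in DASH is plausible. The trial spans four countries and level I to III centers, uses questionnaires in several languages, and leaves the judgement of displacement to each center.

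What is at stake is precision. The confidence limit compared with 10.4 would lie slightly further out than it should, so a truly noninferior result would be missed a little more often than necessary.

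**Working it through.** **Inputs from the Sample size section.** Margin 10.4, SD 14.3, one-sided alpha 0.025, power 90%, 80 evaluable patients, 20% attrition, 100 randomised.

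**Assumptions, since the article gives no figure.** Site ICC of 0, 0.05 or 0.10 for 1-year DASH; 10 or 20 sites; 14.3 is the total SD, including any site variance; true difference zero.

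**Step 1: the plan's own figure.** Per arm, n = 2 × (1.960 + 1.282)² × 14.3² / 10.4² = 2 × 10.51 × 204.49 / 108.16 = 39.7, so 40 per arm and 80 in total; 80 / 0.80 = 100. The plan's figures reproduce. The standard error is 14.3 × √(2/40) = 3.198. Power is Φ(10.4/3.198 − 1.96) = Φ(1.292) = 90.2% by the normal approximation and 89.5% by the noncentral t.

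**Step 2: upper bound, with perfect balance within every site.** The true SE is 3.198 × √(1 − ICC), while a model without site reports about 3.198.

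- Excess SE = 1/√(1 − ICC) − 1
- One-sided error = Φ(−1.96/√(1 − ICC))
- Power without site = Φ((10.4 − 1.96 × 3.198) / (3.198√(1 − ICC)))
- Power with site = Φ(10.4 / (3.198√(1 − ICC)) − 1.96)

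| ICC | Excess SE | One-sided error | Power without site | Power with site |
|---|---|---|---|---|
| 0 | 0% | 2.5% | 90.2% | 90.2% |
| 0.05 | 2.6% | 2.2% | 90.8% | 91.6% |
| 0.10 | 5.4% | 1.9% | 91.3% | 92.9% |

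**Step 3: realistic balance.** Small sites leave blocks unfinished, and attrition breaks balance further. The simulation randomised 100 patients in site-stratified blocks of 2 and 4, analysed a random 80 at a single 1-year visit, and fitted models without site and with a random site intercept (4,000 replicates per row).

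| Sites | ICC | Model SE / empirical SE, no site | CI width, no site → random site | Power, no site → random site |
|---|---|---|---|---|
| 10 | 0 | 3.19 / 3.22 | 12.72 → 12.61 | 88.5% → 88.8% |
| 10 | 0.05 | 3.18 / 3.15 | 12.67 → 12.38 | 89.4% → 90.3% |
| 10 | 0.10 | 3.17 / 3.10 | 12.62 → 12.11 | 90.0% → 91.7% |
| 20 | 0 | 3.19 / 3.26 | 12.69 → 12.55 | 89.0% → 89.1% |
| 20 | 0.05 | 3.19 / 3.14 | 12.70 → 12.38 | 89.9% → 91.0% |
| 20 | 0.10 | 3.19 / 3.09 | 12.69 → 12.13 | 90.4% → 91.7% |

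Each empirical SE carries a Monte Carlo error of about 1/√(2 × 4,000) = 1.1%, so single SE ratios are noisy. Over these runs and a second set on the same design, the excess SE was 1.0, 1.5, 1.7 and 3.4% at ICC 0.05 (mean 1.9%) and 2.4, 3.1, 3.9 and 4.8% at ICC 0.10 (mean 3.5%). The matching one-sided errors are Φ(−1.96 × 1.019) = 2.3% and Φ(−1.96 × 1.035) = 2.1%.

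The estimate itself hardly changes. With 20 sites its empirical SE is 3.14 in both models at ICC 0.05, and 3.09 against 3.07 at ICC 0.10. The design has already removed most of the site variance; the site term lets the reported SE show it. The random-intercept SE also ran slightly low (3.11 against an empirical 3.14, and 3.05 against 3.07), so part of the narrowing at low ICC is not real.

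**Step 4: site as fixed effects.** With 20 sites, one fixed effect per site changed power from 90.0% to 86.1% at ICC 0 and from 90.8% to 88.5% at 0.05. It gained only at about 0.20 (91.1% to 91.9%).

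**The case against.** The strongest reply is that no planned property fails.

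- **Power and false noninferiority.** A reader might infer that the trial is underpowered or that noninferiority could be claimed falsely. Neither follows. Power was computed without credit for baseline or site, and the one-sided error falls below 2.5% when sites differ. This part of the reply stands in full.
- **Purpose of stratification.** One might say that precision bought by stratifying is thrown away. The Discussion gives another purpose: avoiding a site that allocates only to surgery. The forgone precision is real but was never planned on.
- **Fixation method.** The remarks on hook plates look like evidence for a site effect. They concern mainly the surgical arm, so they describe a treatment effect that may differ by site. A site intercept does not model that.
- **Size.** The ICC is unknown and may be near zero. Baseline DASH is already in the model, and the article describes the DASH as cross-culturally adapted in all four countries, so stable differences in scoring between sites may be partly absorbed. The perfect-balance figures in Step 2 are upper bounds. This stands, and is why the simulated range is used below.
- **The SAP.** It may yet add site. That is possible, but the article does not leave the covariates open: it lists them, and the list omits the stratification factor. The mismatch is in what is stated.

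**Conclusion.** The point holds as a minor one. The listed primary model does not match the stratified randomisation, and its interval is somewhat too wide whenever 1-year DASH differs between sites. With 80 patients analysed, 10 or 20 sites and a total SD of 14.3:

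- ICC 0: no effect;
- ICC 0.05: about 1.5–2.5% excess SE and about 1 power point;
- ICC 0.10: about 3–5% excess SE and 1–2 power points.

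The one-sided error stays at about 2.0–2.5%. These sizes rest on the assumed ICC and on a single-visit approximation without the baseline covariate; a lower site ICC after baseline adjustment would shrink them.

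**What to change.** Add site as a random intercept to the primary mixed model and to the VAS model that shares its method. State this in the SAP before unblinding, with a fallback such as pooling small sites or using country if the site variance cannot be estimated. The fallback recovers less precision. Do not use one fixed effect per site, given the few patients expected at each.

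The cost is one model term and a sentence or two in the SAP. The downside is small but not nil: the site variance may be estimated at zero or the model may fail to converge. This is likeliest in the per-timepoint ordinal models, where site adjustment should be optional. Whether the treatment effect differs by site through the fixation method is a separate question and would need its own supportive analysis.

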#### Baseline data

The baseline data collected includes patient demographics such as sex, age, work (and work status), arm dominance, height/weight, tobacco and alcohol habits, and list of current diseases, American Society of Anesthesiologists (ASA) grade, mechanism of injury, radiographs, previous surgeries and injuries in the affected shoulder. The following baseline questionnaires will be filled in digitally: Preinjury Disabilities of the Arm, Shoulder and Hand (DASH), University of California, Los Angeles (UCLA) activity scale, European Quality of Life, 5 Dimensions, 5 Levels (EQ-5D-5L) scores. Shoulder pain via an 11-point visual analog scale (VAS).

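### The primary model's claim to be unbiased under data missing at random also needs a baseline-DASH slope that is constant over visits; a baseline-by-visit term removes that unstated condition

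*Protocol article*

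**What the plan says.** The Statistical analysis section specifies "linear regression for all observed post-randomization measurements, with the participant as a random effect", with fixed effects given as "the baseline DASH score, randomized treatment, visit number, and the treatment–visit interaction as fixed covariates". The treatment-by-visit interaction is spelled out; a baseline-by-visit interaction is not listed.

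The section then states: "The primary model is unbiased for data that are missing at random conditional on the treatment arm, baseline", and adds as a further condition a normally distributed participant-level mean DASH, adjusted for baseline and visit. The planned sensitivity analyses address nonrandom missingness, and imputation is ruled out.

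The Baseline data section names the questionnaire as "Preinjury Disabilities of the Arm, Shoulder and Hand (DASH"), so the covariate is apparently the preinjury score. This is not beyond doubt: the Outcome timepoints section lists "preinjury, baseline, 6 weeks, 3 months, 6 months, 1 year, 2 years, and 5 years", with preinjury and baseline as separate entries, and the visit figure is not shown. On how baseline relates to later scores, the Sample size section says only that "we have limited data on the correlations between the baseline and on-treatment DASH values".

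**The concern.** With one slope for all visits, the model adjusts the 1-year comparison by a slope averaged over visits. Randomization balances baseline at entry, so with complete data the constraint causes no bias. With dropout, the participants still observed at 1 year may differ in baseline between arms. The adjustment then has to carry the correction, and it does so fully only if the 1-year slope is right. The random intercept cannot help, because it is constant over visits and cannot absorb a slope that changes by visit.

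A changing slope is plausible if the covariate is the preinjury score. Preinjury function may say little about DASH at 6 weeks, when the fracture dominates, and more at 1 year. Any resulting bias would arise under missingness at random given arm and baseline, which the plan presents as harmless. The sensitivity analyses, aimed at nonrandom missingness, are not directed at it. At stake is the 1-year noninferiority estimate.

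**Working it through.** **1. The plan's own figures.** Inputs from the Sample size section: margin 10.4, SD 14.3, one-sided alpha 0.025, power 90%, attrition 20%.

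- n per arm = 2 × (1.960 + 1.282)² × 14.3² / 10.4² = 39.7, so 40 per arm and 80 in total. 80 / (1 − 0.20) = 100. Both stated figures reproduce (the exact t-test gives 89.5% power at 80).
- SE of the difference = 14.3 × √(2/40) = 3.2. It is used in step 5.

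**2. Why a common slope can bias the 1-year difference.** To a first approximation,

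bias ≈ (1-year slope − common slope) × (difference between arms in mean baseline among those still observed).

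Both factors must be non-zero. Hand check with assumed slopes 0.1/0.25/0.45/0.6 at the four visits, baseline SD 10, and 20% dropout rising with baseline (log-odds 1 per SD) in one arm only. The fitted common slope is about 0.33. Those remaining in the affected arm have a mean baseline about 0.17 SD lower, or 1.7 points. So (0.60 − 0.33) × (−1.7) ≈ −0.5 points, in line with the simulated values below.

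**3. Simulation with visit-specific slopes.** Assumptions, none of them given in the protocol: random-intercept model, four visits (6 weeks to 1 year), true difference zero, intercept SD 9 and error SD 11.1 (total about 14.3), 20% dropout with log-odds 1 per SD of baseline. Bias of the planned model at 1 year for baseline SD 5 / 10 / 15:

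| Slopes over visits | Same dropout mechanism in both arms | One arm only | Opposite directions |
|---|---|---|---|
| Equal, 0.4 | about 0 | about 0 | about 0 |
| Moderate, 0.1 to 0.6 | about 0 | −0.3 / −0.4 / −0.9 | −0.5 / −1.2 / −1.6 |
| Strong, 0 to 0.9 | about 0 | −0.5 / −1.2 / −1.4 | −1.0 / −2.0 / −3.0 |

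Monte Carlo standard errors are 0.05 to 0.11. With the interaction, estimates lie between −0.23 and +0.15 with no pattern. A larger rerun of the unequal-slope, arm-differential cells agreed within 0.2 points for the planned model and put the interaction model within 0.07 of zero. The sign follows the dropout: moving the pattern to the other arm reverses it.

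**4. Other assumptions.**

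- Baseline correlations rising from 0.1 to 0.5 or 0.6, dropout log-odds 1 to 1.5 per SD in one arm and none in the other: −0.65 to −1.33 points.
- The same correlations, one-arm log-odds 0.4: about 0.25 to 0.45 points.
- The same correlations, log-odds 1 in one arm and 0.5 in the other: about 0.2 to 0.4 points.
- Flatter correlations (0.1/0.15/0.2/0.3), log-odds 1 to 1.5: about 0.1 to 0.45 points.

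**5. Effect on the one-sided error at the margin**, if the bias favours noninferiority: Φ(−1.96 + bias/3.2).

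- 0.2 points: Φ(−1.90) = 2.9%
- 0.4 points: Φ(−1.84) = 3.3%
- 1.2 points: Φ(−1.59) = 5.7%
- 1.6 points: Φ(−1.46) = 7.2%

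A bias of the opposite sign lowers the error and costs power instead.

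**6. Precision (N = 100, complete data, model SE, planned versus interaction).**

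- Equal slopes: 2.86–2.87 versus 2.87–2.88, so the interaction costs about 0.01.
- Moderate slope change: the planned SE is 0–2% larger (at most 2.91 versus 2.86).
- Strong slope change: 1–6% larger (at most 3.03 versus 2.86).
- Equal slopes with dropout: the interaction costs 0.01 to 0.05 (at most 3.15 versus 3.20).

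**The case against.** The strongest reply is that the unbiasedness sentence ties itself to the model's own adjusted mean, and so can be read as the usual statement that a correctly specified model is unbiased under data missing at random. On that reading only a proviso is left implicit. This is fair, but the proviso matters: the listed covariates fix a constant slope, and the Sample size section concedes that little is known about the correlations on which it depends.

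Second, both conditions for bias are assumptions. No passage gives a slope pattern, or a dropout pattern by baseline and arm. A log-odds of 1 to 1.5 per SD in one arm and none in the other is an odds ratio of 2.7 to 4.5 (e¹ to e¹·⁵), which is steep. With 50 per arm, 20% attrition is about 10 people per arm. This stands, and it limits what can be said about size.

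Third, a detailed SAP is still to come. That makes the change easy, but the point is not about missing detail: the article lists the fixed effects and states the property.

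A reader might go further than the documents allow in three ways:

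- That the averaged slope is certainly too flat at 1 year. This needs a preinjury covariate and a slope that rises with time; the first is only apparent and the second is not documented.
- That precision is certainly lost. With equal slopes there is none to gain.
- That the VAS model, which copies the primary one, has the same fault. The Baseline data section lists pain apart from the preinjury scores, so the rationale does not carry over, and no VAS calculation supports it.

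**Conclusion.** The point holds in conditional form. As written, the primary model is unbiased under the stated missing-at-random condition only if the baseline-DASH slope is also the same at every visit. If it is not, and baseline-dependent dropout differs between arms, the 1-year difference can be biased in either direction.

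The documents do not determine the size. It is about 0 with equal slopes or a shared dropout mechanism, and roughly 0.2 to 1.6 points under mild to moderate assumptions. That is 2% to 15% of the margin (0.2/10.4 and 1.6/10.4). Values towards 3 points need strong slope change, a wide baseline spread and dropout running in opposite directions together.

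It would be wrong to conclude that the trial's noninferiority test has an inflated error rate. Error rates of 4–6% follow from particular simulated patterns for which the protocol gives no evidence. The sample size is also untouched, because it rests on an unadjusted t-test. Severity is minor to moderate: a property of the primary analysis is stated too broadly, and it can be secured cheaply before the SAP is final.

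**What to change.** Add the baseline-DASH-by-visit interaction to the fixed effects of the primary model, and continue to read the treatment difference from the 1-year visit. State in the SAP which DASH score, preinjury or post-injury, is the baseline covariate. The unbiasedness statement then no longer needs a constant slope.

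The cost is one line in the SAP, three extra parameters for the four visits to 1 year, and no new data. If slopes are in fact equal, the SE rises by about 0.01 with complete data and by up to 0.05 in the simulated dropout patterns. No change to the sample size is needed.
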